### Outcome measures

The primary outcome of this study is physical activity. Physical activity will be measured objectively with the StepWatch™Activity Monitor 3.0 (StepWatch) (Cyma Corporation Seattle WA, USA) as well as subjectively with self-reports: the Activity Questionnaire for Adults and Adolescents (AQuAA), and the Children's Assessment of Participation and Enjoyment (CAPE).

*The StepWatch *is an ankle-worn bi-axial accelerometer (frontal-sagittal plane) that registers the number of steps per minute. The StepWatch can accurately record steps for different gait styles, because the sensitivity settings are calibrated for each child individually. Before each registration period, the sensitivity settings will be calibrated by comparing manual counts of a 50-step walk with StepWatch recordings. The settings will be adjusted until an agreement of > 95% is reached between manual counting and the StepWatch registration. Children will wear the StepWatch for seven consecutive days during all waking hours, except when swimming and bathing. During the registration period, the parents will fill in a weekly diary to register the child's daily activities and the weather conditions. The StepWatch is valid for children with CP, and able to discriminate between activity levels of children with different GMFCS levels[7].

*The AQuAA *is a reliable questionnaire to assess physical activity as well as sedentary behavior[35] in adolescents and adults. It is derived from the valid and reliable Dutch Short Questionnaire to Assess Health-Enhancing Physical Activity[36], but questions about sedentary behaviours were added and the recall period was specified as "the past seven days"[35]. The parents will have to rate how many days, and how much time per day the child spent on transportation to and from school, activities at school and at home, as well as leisure time activities and sports in the past seven days. The parents will also have to indicate how strenuous (light/moderate/vigorous) these activities were. For the purpose of the present study the examples of activities will be adapted, so that they are relevant for school-aged children.

*The CAPE *is a 55-item questionnaire that will be used to assess the frequency of participation in activities outside school hours[37]. The parents will be interviewed to rate the child's frequency of participation in the past four months in five types of activities (recreational, active physical, social, skill-based, and self-improvement activities). The frequency, scored on a 7-point scale, provides: a) the overall participation scores, b) the domain scores for formal and informal activities, and c) the scores for participation in each type of activity. The Dutch version of the CAPE is a valid and reliable questionnaire with which to assess the participation of children with disabilities aged 6-21 years[38].

Secondary outcomes are fitness, capacity of mobility, social participation, and health-related quality of life. Fitness is defined in this study as isometric muscle strength, aerobic capacity, anaerobic capacity, and anthropometry. Capacity of mobility is defined as gross motor functioning, functional muscle strength, and walking capacity. Health-related quality of life is as CP-related quality of life, self-reported fatigue, self-perception, and attitude towards physical activity.

*Isometric muscle strength *of the knee extensors and hip abductors will be assessed with a hand-held dynamometer (HHD)[39] (MicroFet, Biometrics, Almere) using the "make-method". The assessor stabilizes the dynamometer at the limb while the child pushes as hard as possible against the dynamometer for three seconds. Peak strength (N) is then read from the dynamometer, and the distance from the knee and hip joint to the dynamometer is measured to determine the lever arm. Moment is then calculated from peak strength and lever arm (Nm). After one practise trial, the children will perform three test trials. The means of the peak moment (Nm) over three trials will be used for the analysis. The testing positions and stabilization have been described in detail elsewhere[32].

*Aerobic capacity *will be assessed during an all-out continuous progressive cycling test on a bicycle ergometer specifically adapted for children with CP (adjustable cranks, shoe fixation, pediatric saddle) (Corival V2 Lode B.V., Groningen, the Netherlands). After a 5 to 7-minute warming-up, the initial workload will be determined, based on heart-rate (105-150 beats/min). During the test the workload will be increased every minute (1-15 Watt), based on body height and GMFCS level (range: from 0-3 Watt for GMFCS III and body height < 120 cm, to 10-15 Watt for GMFCS I/II and body height >160 cm). The children have to cycle at a constant speed (50-70 rpm), and will be verbally encouraged to keep on cycling until exhaustion. The criteria for maximal exercise are: 1) heart-rate ≥ 180 beats/min, or 2) respiratory exchange ratio (RER) ≥ 1.00, and 3) subjective signs of exhaustion. Pulmonary gas-exchange will be measured with the Quark CPET system (Cosmed, Rome, Italy) and the corresponding software (PFT CPET Suite, version 9.1a, Cosmed S.r.l, Rome, Italy) to determine breath-by-breath oxygen uptake and carbondyoxide output. Heart-rate will be measured with a Cosmed heart-rate monitor (Cosmed, Rome, Italy). Maximal oxygen uptake (VO2max) will be calculated as the highest mean values over a 30-second interval, expressed per kilogram bodyweight (ml/kg/min). Peak power (Watt) is the highest power output (maintained for at least 30 seconds) that is achieved during the test.

*Anaerobic capacity *will be assessed with the 20-second Wingate anaerobic test (WAnT20) (Wingate Software V1, Lode B.V., Groningen, the Netherlands), adapted from the original 30-second test[40], on the same bicycle ergometer. During a 4-minute warming-up, the children will perform two or three 5-second sprint practise trials to determine the optimal torque for the WAnT20, by varying the braking force (Nm) between the practise trials. After the practise trials, the children will rest for three minutes before they perform the WAnT20. They will start with one minute of comfortable cycling at 60 rpm, after which they will cycle as fast as possible for 20 seconds against the constant optimal braking force. Mean power (Watt) over 20 seconds expressed per kilogram bodyweight will be calculated as an estimate of anaerobic capacity, and used for the analysis.

*Anthropometry measures *consist of height, bodyweight, and skinfold thickness. Height and bodyweight will be used to calculate the body mass index as weight in kilograms divided by height in meters squared. Triceps and subscapular skinfold of the non-dominant arm (diplegia) or non-affected side (hemiplegia)[41] will be measured with a Holtain skinfold caliper (accuracy 0.2 mm), according to the protocol of Tanner et al.[42]. The mean skinfold thickness over three measurements per site will be used for the analysis.

*Gross motor functioning *will be evaluated with the Gross Motor Function Measure 66-item set (GMFM-66-IS)[43] which is a validated and shortened version of the GMFM-66[44]. To determine the GMFM-66-IS, the child is observed in a standardized environment, and gross motor functioning is rated on a 4-point scale by a trained assessor. The Gross Motor Ability Estimator (GMAE) software will be used to calculate the GMFM-66 interval scores (ranging from 0-100).

*Functional muscle strength *of the large muscle groups of the (most) affected leg will be evaluated by two functional exercises[45]: the 30-second lateral step-up test, and the 30-second STS test. The children will be instructed to perform as many step-ups or STSs as possible during a period of 30 seconds. If necessary, balance support will be provided. The number of repetitions performed during each test will be used for the analysis.

*Walking capacity *will be evaluated with the 1-minute walk test (1MWT)[46] on a flat, non-slippery 51-meter circular walking track. Each meter is marked with adhesive tape to make it easy to calculate the completed distance. The child will be instructed to walk for one minute as fast as possible, without running. After one minute the meter nearest to the child's position will be recorded and the total distance completed will be used for the analysis.

*Social participation *will be assessed with the Life-Habits for children[47]. Six domains of participation (fitness, personal care, housing, mobility, education, and recreation) will be assessed by means of an interview with one of the parents. The parent will have to rate: 1) the level of difficulty the child has in performing each of 36 life habits (5-point scale), and 2) the type of assistance the child needs to perform that life habit (4-point scale).

*CP-related quality of life *will be assessed with the CP-Quality of Life questionnaire[48] as a proxy parent-report. Five domains will be measured (social well-being and acceptance, functioning, participation, emotional well-being, pain and impact of disability) resulting in a total of 53 questions. The questions start with: 'How do you think your child feels about...?', and are scored on a 9-point scale.

*Self-reported fatigue *will be assessed with the PedsQL Multidimensional Fatigue Scale[49,50]. Three domains will be assessed (general fatigue, sleep/rest fatigue, and cognitive fatigue), and each domain contains six questions that start with: 'In the past month, how much of a problem has this been for you?'. The questionnaire (5-point scale) will be completed by the child, with help from the parents if necessary.

*Self-perception * will be assessed with Harter's Self Perception Profile for Children[51], adapted for children with CP[52]. The children will be assessed on three domains (motor competence, athletic competence, and global self-worth). Each domain has eight items, consisting of two opposite statements, such as "Some children think they are strong" and "Other children think they are not so strong". The children will be asked in an interview to choose which child they resemble most, and to indicate whether they are somewhat similar or very similar.

*Attitude towards physical activity *will be assessed in both the children and the parents by means of self-report. The children will have to indicate to what extent they agree with each of 14 statements, previously used in an intervention to improve physical activity in typically developing children[53]. The statements reflect eight advantages and six disadvantages of sport, for example "If I do sports, I have fun". Each statement is scored on a 5-point scale. The parents will have to indicate their opinion with regard to sports, and to what extent they agree with each of seven statements related to the accessibility of sports clubs, for example "I think my child is not good enough to join a sports club". Each statement is scored on a 5-point scale.

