### Design

This study will be a 6-month single-blinded randomized controlled trial (RCT) with a 6-month follow up, that will be performed in special schools for children with disabilities and pediatric physiotherapy practices in the Netherlands, between September 2009 and February 2012. Within each school or practice, participants will be randomly assigned to either the intervention group or the control group. A blinded independent researcher will provide the allocation sequence in sealed envelopes. For schools and practices with five or more participants, children will be stratified for GMFCS level (I *vs*. II/III) before randomization. Group allocation will only be revealed to the parents after the baseline measurements. The assessors are blinded for group allocation during the entire study period. The children and parents will be instructed not to tell the assessors which group they are assigned to. The study protocol has been approved by the Medical Ethics Committee of the VU University Medical Center in Amsterdam.

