Counseling is aimed at motivating the child and the parents to adopt a more active lifestyle. It consists of one or two home visits, parents visiting the fitness training, a sports workshop for the children, and one or two follow-up telephone calls. During the home visit and follow-up telephone calls the child and the parents will receive counseling, based on the Motivational Interviewing technique[27]. This is a directive and client-centered interview style that is intended to bring about behavioral change, like achieving a more active lifestyle. During the counseling, the interviewer will introduce some basic lifestyle themes (such as satisfaction with present lifestyle, and attitude towards a more active lifestyle), and will try to elicit statements concerning desire, ability, and reasons and need for changing the present lifestyle[27]. During this process the interviewer will not challenge resistance to change, but will go along with the resistance and will explore the ambivalence of the child or the parents with regard to a change in lifestyle. The interviewer then will structure possible ambivalence, in order to help the child and the parents to prioritize arguments for changing ('change talk') or not changing. When there is sufficient motivation for change, the interviewer will change the focus of the counseling to reinforce 'change talk' and to help the child and the parent to set specific goals for achieving an active lifestyle.

Home-based physiotherapy is aimed at increasing the capacity of daily activities in the home situation, in the playground or at school. The child will receive training in certain daily activities, based on the mobility problems indicated by the child and/or the parents (such as getting into the car, going up stairs carrying something, and skating). The physiotherapist will make a maximum of four visits, starting when the frequency of the fitness training has decreased to once a week (see Figure 1).

Whether or not the lifestyle intervention has been successful, will be evaluated only in the intervention group by means of the problem score and the stages of change according to Prochaska et al.[28].

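### Both subjective primary instruments (AQuAA and CAPE) are rated by unblinded parents who are counselled in one arm only, and the CAPE recall at T6 covers programme time

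*Protocol article*

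**What the plan says.** Under Outcome measures in the Protocol article, physical activity is the primary outcome and has three instruments. One is objective: "Physical activity will be measured objectively with the StepWatch". The other two are described as measuring activity "subjectively with self-reports: the Activity Questionnaire for Adults and Adolescents (AQuAA), and the Children's Assessment of Participation and Enjoyment (CAPE".

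The same section names the rater of each. For AQuAA: "The parents will have to rate how many days, and how much time per day the child spent on transportation", with a recall of one week ("leisure time activities and sports in the past seven days"). For CAPE: "The parents will be interviewed to rate the child's frequency of participation in the past four months". CAPE is used to "assess the frequency of participation in activities outside school hours".

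The Design section states: "Group allocation will only be revealed to the parents after the baseline measurements". Assessors stay blinded throughout, and families are told not to disclose their group to them. Under Lifestyle intervention: "Counseling is aimed at motivating the child and the parents to adopt a more active lifestyle". Control families continue with regular physiotherapy.

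Fitness training runs for months 0-4 and the lifestyle intervention for months 0-6. Assessments are at T0, T4 (described only as limited measures), T6 and T12. Under Statistical analysis, the treatment effect is the group-by-time interaction, and the sample size is based on steps per day.

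**The concern.** A parent rating is not a self-report by the child. The article itself uses the term proxy parent-report for the CP quality-of-life questionnaire, so the label on the two primary instruments does not match its own usage.

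The label matters less than who rates and when. The rater is blind at T0 and unblinded at every later visit, and in one arm the programme works directly on the rater's attitude to the behaviour being rated. A change in how parents report, with no change in what the child does, would appear in the change from baseline and so in the estimated treatment effect. Single blinding here means that assessors are blinded. That limits interviewer bias but leaves the source of the rating unprotected.

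CAPE has a second problem. Its four-month recall at T6 looks back over months in which the programme was running, so programme activities held outside school hours could be scored as outcome.

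At stake is the case where a parent rating is positive and StepWatch shows nothing. With all three instruments primary, that could be presented as increased physical activity, although expectation or the programme sessions themselves might explain it.

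**Working it through.** **1. Who rates, and what they know**

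| Instrument | Source of the rating | Knows allocation at T0 | Knows allocation after T0 | Counselled in one arm only |
|---|---|---|---|---|
| StepWatch | Device | not applicable | not applicable | not applicable |
| AQuAA | Parent | No | Yes | Yes |
| CAPE | Parent, interviewed | No | Yes | Yes |

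Write the expected change in a parent rating as true change plus reporting change. The group-by-time effect then estimates (difference in true change) + (difference in reporting change). The T0 rating is made blind, so adjusting for it does not remove the second term.

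**2. Recall windows against the programme calendar**

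The CAPE window at visit T is months T-4 to T.

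- T6: months 2-6. Overlap with the lifestyle intervention (0-6) is 4 of 4 months. Overlap with fitness training (0-4) is 2 of 4 months, the once-weekly phase.
- T12: months 8-12. Overlap with either component is 0.
- T4: months 0-4, full overlap, but only if CAPE is given then, which the article does not say.
- AQuAA at T6 covers seven days, about two months after training ended, so training sessions cannot enter it. The overlap point concerns CAPE alone.

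**3. The plan's own figure**

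The article requires 22 per group for 1,000 steps per day with power 0.8 and alpha 0.05. It prints no standard deviation, so the 22 cannot be reproduced, only back-solved. With a two-sided test (assumed), SD = 1000 × √(22/2) / (1.960 + 0.842) ≈ 1,184 steps per day, or about 1,157 with the t distribution. The step from 22 to 25 matches 12% drop-out: 22/0.88 = 25. Neither figure is disputed; 22 is used below only as the number per arm.

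**4. What a reporting shift would do (illustration)**

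The documents give no size for a shift, so 0.1, 0.25 and 0.5 SD are assumed. Two-sample t-test, no true effect, n = 22 per arm, 42 degrees of freedom, two-sided critical value 2.018, noncentrality = d × √(22/2).

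| Shift d (SD) | Noncentrality | False-positive rate, one measure | Either of two, if independent: 1-(1-p)² |
|---|---|---|---|
| 0 | 0 | 5.0% | 9.75% |
| 0.10 | 0.33 | 6.2% | 12.0% |
| 0.25 | 0.83 | 12.8% | 24.0% |
| 0.50 | 1.66 | 36.7% | 60.0% |

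The last column starts at 9.75% with no shift, so at 0.1 SD most of the 12.0% is multiplicity. Two ratings by the same parent are likely to be positively correlated, which lowers that column. The calculation uses a t-test in place of the planned random coefficient analysis.

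**The case against.** Families cannot practicably be blinded to a counselling and training programme, and pairing an objective with a subjective measure is a defensible design. Assessors are blinded, so the CAPE interviewer should not add bias. The measure that sets the sample size is not parent-rated. StepWatch also comes off for swimming, and the questionnaires cover sport and leisure that it cannot record, so a positive questionnaire beside a null StepWatch result is not necessarily an artefact. All of this stands. It argues for keeping the parent ratings and presenting them, but not for giving them equal weight in the primary claim.

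Three stronger readings are tempting, and the article does not support them.

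- A reader might infer that both ratings are biased towards benefit. That direction is likely but not shown: counselled parents could also become stricter raters.
- A reader might infer that programme sessions do inflate CAPE. CAPE covers time outside school hours, the trial runs in special schools and physiotherapy practices, and the article does not say when sessions take place or whether any item would count them. Training was also cut to once a week to make room for activities such as a sports club, which CAPE is properly meant to detect.
- A reader might extend the overlap to AQuAA, to T12 or to T4. It does not apply to the first two, and the content of T4 is not stated.

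It can also be said that rules on outcome hierarchy and interviewer instructions often sit in a fuller protocol or manual. That is fair, and their absence is not the point here. The rater, the label, the unblinding and the primary status are all stated in the article.

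**Conclusion.** The point holds as a risk of differential reporting in two of the three primary instruments. It follows from four stated facts: parents rate AQuAA and CAPE; they are blind only at baseline; one arm's parents are a target of the counselling; and the effect is read from change over time. Blinded assessors do not remove it.

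The CAPE overlap at T6 is also established as a matter of calendar: four of four recall months within the lifestyle intervention and two of four within training. Whether it alters the score is possible, not shown.

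The size is unknown. The 6%, 13% and 37% per-measure rates rest on assumed shifts, 22 per arm and a simple t-test, and show sensitivity only. The 60% for either measure should not be quoted without its 9.75% starting point and the independence assumption.

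Nothing here reaches StepWatch, so the primary outcome as a whole is not undermined. The matter is worth correcting because the changes are small and bear on what may be claimed.

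**What to change.** - Describe AQuAA and CAPE as parent-reported wherever they are called self-reports.
- Name StepWatch steps per day as the lead primary measure and read AQuAA and CAPE as supportive. State that a positive parent rating with a null StepWatch result will be reported as parent-reported change only, and not as a demonstrated increase in activity.
- Give CAPE interviewers one instruction, identical in both arms, not to count study sessions, physiotherapy sessions or the sports workshop. Word it neutrally so that applying it does not reveal the allocation.
- Use CAPE at T12 as the programme-free reading, and note beside the T6 result that its window covers programme time.
- Add the unblinded, counselled rater to the limitations in the Discussion, which at present names only that effects cannot be attributed to a single component.

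The cost is wording and one line of interviewer instruction; no data collection changes. The downside is that fewer measures carry the primary claim, and StepWatch does not record swimming. The parent reports should therefore still be presented beside it, so that a real gain in activity without steps can be seen.

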### Statistical analysis

A sample-size calculation revealed that at least 22 children in each group are required to detect a difference in improvement of 1,000 steps per day between the intervention and the control group on the primary outcome. The power was 0.8, and the alpha was set at 0.05. This increase in steps per day seems to be clinically relevant, since improved health outcomes have been reported in adults after an increase of 1,000 in the amount of steps per day[54]. Taking into account drop-outs, 25 children will be included in each group.

Student *t*-tests will be performed to evaluate group differences at baseline, and a random coefficient analysis[55] will be performed to determine differences in change over time (treatment effect) between the control group and the intervention group. This method takes the dependency of children within physiotherapy practices and schools into account. An intention-to-treat analysis will be performed. The primary outcome (physical activity) and secondary outcomes (fitness, capacity of mobility, social participation, and health-related quality of life) will be the dependent variables in the analysis, with group allocation (control group or intervention group) and measurement occasion (time) as independent variables. The intervention effect will be evaluated by the group * time interaction. The alpha is set at 0.05. The influence of age, gender, and disease and environmental characteristics on the treatment effect will be investigated, and, if necessary, included as covariates in the analysis. The data will be analyzed with the Statistical Package for the Social Science, version 15.0 (SPSS Inc, Chicago, Illinois, USA).

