To achieve optimal compliance with training, it is important that the children enjoy the training. The fitness training will therefore be performed in groups of two to five children and most of the exercises will be the form of in games. The fitness training will last for four months: twice a week in the first two months, and then once a week in the following two months. The frequency will be reduced to once a week to provide the opportunity to start participating in other physical activities, such as training in a sports club. Each training session will last for one hour, starting with a 5-minute warming-up period. This will be followed by the core part of the training, consisting of two muscle strengthening exercises and three anaerobic exercises. Each training session will end with a cooling down period. Figure 2 presents an overview of a training session. The children wear their usual orthoses or orthopedic shoes during the training sessions. All the physiotherapists will have to attend workshops in which they receive instructions about the fitness training.

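### Small training groups can create clustering in the intervention arm only; a site effect common to both arms would not capture it, and the sample-size statement shows no allowance for it

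*Protocol article*

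**What the plan says.** Four statements in the protocol article bear on this.

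- **Allocation (Design):** "Within each school or practice, participants will be randomly assigned to either the intervention group or the control group". A site can therefore hold both arms.
- **Delivery (Fitness training program):** "The fitness training will therefore be performed in groups of two to five children". The training lasts four months. Under Procedure, controls keep their usual physiotherapy, and no trial training groups are described for them.
- **Sample size (Statistical analysis):** "at least 22 children in each group are required to detect a difference in improvement of 1,000 steps per day". Then: "The power was 0.8, and the alpha was set at 0.05". The step up from 22 has one stated reason: "Taking into account drop-outs, 25 children will be included in each group". No SD, ICC or design effect is given.
- **Analysis (Statistical analysis):** the treatment effect is the group-by-time interaction in a random coefficient analysis. On clustering the article says only: "This method takes the dependency of children within physiotherapy practices and schools into account". Training group is not named as a level, and the random terms are not listed.

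**The concern.** The named dependency is not the one that most affects the treatment contrast. With both arms present in a site, an effect shared by all its children is common to the two arm means and largely cancels from their difference. A site intercept that is constant over time also cancels from change, which is what the group-by-time term measures.

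Correlation in how intervention children respond because they share a group does not cancel. There are reasons to expect some. Most exercises are group games, physiotherapists may vary or invent exercises, and the counselling component includes parents visiting the training and a sports workshop for the children. The fitness outcomes are direct targets of the group sessions and are analysed with the same model.

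If this correlation is positive and not modelled, the standard error is too small, the test rejects too often under the null, and a power of 0.8 calculated for independent children is optimistic.

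**Working it through.** **Inputs.** From the article: 22 per arm, a difference of 1,000 steps per day, power 0.8, alpha 0.05, 25 per arm recruited, training groups of 2 to 5. Assumed: a two-sided test, equal group sizes, training groups formed within site, training-group ICC of 0.01 to 0.15.

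**Step 1: the stated 22.** It cannot be reproduced, because no SD is given. Solving backwards with the two-sided normal formula:

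SD = 1,000 / [(1.960 + 0.842) × √(2/22)] ≈ 1,184

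Any SD from about 1,157 to 1,183 rounds up to 22. The step to 25 corresponds to a drop-out of 1 − 22/25 = 12%. The figures are consistent with an ordinary calculation for independent children, but that is consistency and not proof.

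**Step 2: variance with clustering in one arm.** With group size m, the intervention-arm variance is multiplied by 1 + (m − 1) × ICC and the control-arm variance by 1. The variance of the difference is multiplied by

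f = {1 + [1 + (m − 1) × ICC]} / 2

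- m = 2, ICC 0.05: f = (1 + 1.05)/2 = 1.025
- m = 3.5, ICC 0.10: f = (1 + 1.25)/2 = 1.125
- m = 5, ICC 0.15: f = (1 + 1.60)/2 = 1.30

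**Step 3: power.** Power = Φ(2.802/√f − 1.960) at 22 per arm. At 25 per arm, 2.802 becomes 2.802 × √(25/22) = 2.987. For example, at f = 1.30 and 22 per arm: 2.802/1.140 − 1.960 = 0.497, so power is 69%.

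| ICC (assumed) | m = 2: 22 / 25 per arm | m = 3.5: 22 / 25 per arm | m = 5: 22 / 25 per arm |
|---|---|---|---|
| 0.01 | 79.8% / 84.6% | 79.5% / 84.3% | 79.2% / 84.1% |
| 0.05 | 79.0% / 83.9% | 77.6% / 82.6% | 76.2% / 81.3% |
| 0.10 | 78.1% / 83.0% | 75.2% / 80.4% | 72.5% / 77.8% |
| 0.15 | 77.1% / 82.1% | 72.9% / 78.2% | 69.0% / 74.5% |

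**Step 4: does a common site effect repair the standard error?** Two simulations used one change score per child, correlation in the intervention arm only, and a model with site and arm.

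- Site and arm terms, 6,000 runs per setting. Type I error was 5.3% (11 sites, groups of 2, ICC 0.05), 6.4% (7 sites, groups of 3, ICC 0.10) and 9.2% (5 sites, groups of 5, ICC 0.15).
- Random site intercept, 100,000 runs per setting. With 8 sites of 3 + 3 children, type I error was 6.0% at ICC 0.05 and 6.8% at 0.10. With 5 sites of 5 + 5 it was 6.5% and 8.0%. The ratio of model to true standard error was 0.95 and 0.92 in the first layout, 0.93 and 0.89 in the second. With no clustering the same procedure gave 5.4% and 5.2%, with ratios 0.98 in both, so a few tenths of a point belong to the small-sample method itself.

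A site effect shared by both arms therefore does not remove the problem. An analysis of site-level differences between arms kept type I error at about 5% throughout.

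**The case against.** The strongest reply is that the article does not fix the random terms. A random coefficient analysis can include a site-level random coefficient for group or for group by time, and where a site has one training group that would cover this clustering. A condensed article may leave such detail to the full protocol or analysis plan. This stands, and it makes the point about the standard error conditional. It does not remove the point, because the one sentence on dependency names a level that, fitted as a common effect, misses the one-arm correlation.

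Second, a reader might infer that the 22 per group is known to assume independent children. The article does not support that: with no SD or ICC the calculation cannot be rebuilt. What can be said is that no allowance is shown and that drop-out is the only reason given for 25.

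Third, the ICC may be small. Group sessions fall to once a week after two months and end at month 4, before T6 and T12. Home counselling and home-based physiotherapy are tailored to the individual child, and the objective primary measure is steps in daily life. Stratifying only sites with five or more participants suggests that smaller sites are expected, where groups would be nearer two. All of this limits the size. It does not change the direction.

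Fourth, controls at one site may also share a therapist; the article does not say. A common site effect would absorb only what the two arms share, so this does not cover the training groups.

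Finally, the simulations use one change score and not the planned repeated-measures model. They show the mechanism and its order of size, not exact error rates for this trial.

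**Conclusion.** The point holds in conditional form. If the only clustering term is a site effect common to both arms, the standard error of the group-by-time effect will be too small for any positive training-group ICC. For assumed ICCs of 0.05 to 0.15 and groups of two to five, power at 22 per arm is about 79% down to 69%, and type I error runs from roughly 5–6% to about 9%. The worst figures need every intervention child in a group of five at ICC 0.15. Near ICC 0.01 the effect is negligible, and with all 25 per arm retained and an ICC of at most 0.10, power is about 78% or more.

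A reader might conclude that the planned test fails to keep its 5% level, or that the trial is underpowered and must recruit more. Neither follows: the random terms, the SD and the ICC are all unstated. This is a cheap improvement to the analysis, not a demonstrated error in it.

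**What to change.** - Specify a random training-group effect on change (that is, on group by time, not on the baseline level) for intervention children only, with each control child as a cluster of one. Where a site has a single training group, a site-by-arm random coefficient does the same job.
- Use small-sample degrees of freedom, and fix the rule in advance.
- Restate the power as conditional: give the assumed SD and show power for 22 to 25 per arm over a range of training-group ICC.
- Do not enrol more children on this account.

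The cost is one model term, recording each child's training group, and a revised power sentence. The interval becomes slightly wider, and the variance component rests on few groups. Few degrees of freedom carry their own price: the purely site-level comparison in the second simulation had power of 71% (8 sites) and 62% (5 sites) even without clustering, and 67% and 54% at ICC 0.10. A model that keeps control children as individuals should lose less, but that was not calculated here, so the restated power should be computed under the degrees-of-freedom rule actually chosen.
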